#### **8.2.2 Serious adverse events (SAEs)**

A serious adverse event is any untoward medical occurrence or effect that:

- Results in death;
- Is life threatening (at the time of the event);
- Requires hospitalization or prolongation of existing inpatients' hospitalization;
- Results in persistent or significant disability or incapacity;
- Is a congenital anomaly or birth defect; or
- Any other important medical event that did not result in any of the outcomes listed above due to medical or surgical intervention but could have been based upon appropriate judgement by the investigator.

An elective hospital admission will not be considered as a serious adverse event.

The investigator will report all SAEs, that occurred during hospitalization from application until twelve hours after removal of the investigational product, to the sponsor without undue delay after obtaining knowledge of the events:

- Maternal or fetal death for any reason;
- Severe allergic reaction of abdominal patch or application technique that requires hospitalization or prolongation of existing inpatients hospitalization;
- Any unforeseen important medical event as a result of the investigational product that needs medical intervention.

The investigator will report all SAEs to the sponsor without undue delay after obtaining knowledge of the events, except for the following SAEs:

- SAEs or AEs that did occur independently from the investigational product, but as a consequence of a (pregnancy or delivery related) disease, will not be reported to the sponsor. For example, criteria described by neonatal and maternal morbidity, shoulder dystocia, known congenital anomaly or birth defect, dysmaturity, macrosomia, hypoglycaemia, hyperbilirubinemia, feeding problem/weight loss, therapeutic hypothermia, perinatal asphyxia, observation for meconium-stained amniotic fluid, observation for suspected infection, because of maternal medication use in pregnancy, maternal intrapartum fever or maternal hypertensive disorders.
- The Investigator will report the SAEs through the web portal 'ToetsingOnline' to the accredited METC that approved the protocol, within 7 days of first knowledge for SAEs that result in death or are life threatening followed by a period of maximum of 8 days to complete the initial preliminary report. All other SAEs will be reported within a period of maximum 15 days after the sponsor has first knowledge of the serious adverse events.

#### **8.2.3 Follow-up of adverse events**

All AEs will be followed until they have abated, or until a stable situation has been reached.

Depending on the event, follow up may require additional tests or medical procedures as indicated, and/or referral to the general physician or a medical specialist.

SAEs need to be reported till end of study within the Netherlands, as defined in the protocol.

#### **8.2.4 Data Safety Monitoring Board (DSMB) / Safety Committee**

Not applicable

## 9. STATISTICAL ANALYSIS

### 9.1 Primary study parameter(s)

Primary data statistical analyses will be performed using SPSS version 29 (IBM Corp., Armonk, NY, USA) and SAS software version 9.4 (SAS Institute Inc., Cary, NC, USA). Signal quality will be defined as the percentage of time (minutes) in which the remote eCTG device delivers an FHR value. Signal quality will be determined for each patient. Mean, SD, and 95% confidence interval (CI) of the mean success rate will be calculated using a one-sample t-test. The one-way ANOVA analog, Kruskal-Wallis test will be used in when no normal division of outcomes is found. Success rate will be defined as the number and percentage (N/%) of remote eCTG registration the first day of inclusion with at least 30 minutes interpretable signal quality and/or less than 20% signal loss during 30 to 90 minutes measurement (see section 7.1.1).

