### Remote electrophysiological cardiotocography monitoring (eCTG) – Nemo Remote® (NRM)

Due to the limitations of conventional CTG monitoring, extensive research has been carried out to develop new, non-invasive, monitoring methods. Remote eCTG – including NI-fECG – monitoring has shown to be a very promising technique (17-20). This technique uses a wireless and beltless electrode patch that is placed on the maternal abdomen (Figure 1). It monitors fetal heart rate (FHR) by fetal electrocardiography (fECG), maternal heart rate by maternal electrocardiography, and the electrical activity of the uterine muscle by electrohysterography (EHG) (21-24). The electrophysiological recordings are hardly affected by maternal or fetal movement or abdominal wall thickness, as they are transferred through conduction of electrical signals across the underlying tissues (13, 25). Furthermore, the wireless electrode patch on the maternal abdomen gives patients the ability to move (16). The HASTA study will evaluate the feasibility of self-administered home monitoring in a Home@Hospital setting for a selected groups of complicated pregnancies. Feasibility will be evaluated by assessing the success rate (percentage of successful measurements) of remote eCTG, and whether no switch to conventional CTG due to interpretability is needed. Success rate is defined as maximum of 20% signal loss of total recorded time or at least 30 minutes of sufficient CTG interpretability. For further description see sections 2.1 and 7.1.1.

[figure not shown][figure not shown]

*Figure 1. eCTG including NI-fECG – Nemo Remote® (NRM)*

Furthermore, the FHR obtained from the fetal ECG measurements collected through NRM in this study will be used to check if the algorithm of the FHR – developed during labor – can also benefit for premature fetus. Automated interpretation of fetal monitoring could lead to improved prevention in the future. In addition, the effects of self-administered remote eCTG monitoring in a Home@Hospital setting on maternal and perinatal outcomes, patient and HCP satisfaction, and costs will be evaluated.

Besides feasibility of eCTG, this study will additionally evaluate the feasibility of synchronized multimodal acquisitions of maternal and fetal measurements as a first step towards the development of a prediction model.

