#### 6.4.4 Clinical warnings and potential risks

- The system is not a replacement for observation and evaluation of the patient and fetus at set times by a qualified healthcare provider, who makes diagnoses and takes decisions regarding treatment and interventions. For accurate care of the patient and fetus, clinical assessment of the CTG should be combined with knowledge of patient anamnesis and risk factors.

- The system is not designed for:
  - Use during defibrillation, electrosurgery or magnetic resonance imaging (MRI)
  - Use in x-ray departments.

Remove the Patch prior to performing any of the above scenarios, otherwise harm to the patient or damage to equipment may occur.

- From 27 to 36 weeks gestational age, the chance of FHR signal loss is higher due to the presence of vernix caseosa, which can reduce transmission of electrical signals.
- In case clinical decision-making cannot be properly substantiated based on the CTG registration, other observation and monitoring methods must be used.
- In some cases, the use of the Patch, in combination with skin prep, may result in skin irritation. Try to reduce the duration of use and the skin prep as far as possible if the skin is irritated.
- To prevent reduced performance, replace a Patch when its adhesive properties have reduced or the electrode gel has come partially loose.
- To prevent cross-contamination, never reuse a Patch on another patient.
- To prevent the risk of skin irritation, ensure that no cleaning or disinfection agent residues remain on the system.
- The system detects repeating characteristics of the fetal and maternal ECG signal to calculate the fetal and maternal heart rate. If either the pregnant woman or her fetus has a highly irregular ECG, the heart rate may not be calculated correctly and the system may temporarily provide incorrect output. In case clinical decision-making cannot be sufficiently substantiated, other observation and monitoring methods must be used.
- In rare cases, the amplitude of the fetal ECG signal that is measured on the maternal abdomen is in the same order of magnitude as the amplitude of the maternal ECG that is being measured. In these circumstances, interchange of fetal and maternal heart rate may occur. The system will then temporarily display FHR values as maternal heart rate and maternal heart rate values as FHR. In case clinical decision-making cannot be sufficiently substantiated, other observation and monitoring methods must be used.

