## 7. METHODS

### 7.1 Study parameters/endpoints

#### 7.1.1 Main study parameter

To assess the primary objective of successful remote eCTG monitoring, definitions of successful measurement are as follows:

- Minimum of 30 minutes eCTG registration (32);
- Including overall a maximum of 20% signal loss (32);
- Sufficient interpretability according to HCPs clinical interpretation, if not maximum extended until 90 minutes when reassuring but insufficient.

Criteria defining a successful measurement is described in a standard operating procedure (SOP) and will be available for (trained) HCPs at the hospital to avoid prematurely closing of the eCTG registration. The precise duration of monitoring in minutes, the amount of signal loss in percentage and the duration of signal loss in minutes will be derived from the recordings during the analysis phase of the project, i.e. not during the measurements.

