#### 7.1.2 Secondary study parameters

##### *Remote eCTG parameters*

- Number of days with remote monitoring per participant.
- Number of remote eCTG measurements per participant.
- Need to repeat remote measurements the same day because of reassuring but insufficient interpretability.
- Number of switch to conventional CTG and possible maternal and/or fetal reason.
- Number of switch to conventional CTG needed because of poor signal of remote eCTG measurement and possible cause.
- Success rate of CTG measurement after switch based on same criteria as in remote eCTG monitoring (7.1.1).
- Incidence of skin irritation.
- Number of “unscheduled visits” and reason.
  - When there is an indication for an additional visit in-hospital as if the participant is monitored at home (e.g. contractions, decreased fetal movements, PE symptoms, suspicion of PPRM).
- Number of “re-admissions” and reason.
  - When there is an indication of admission as if the participant is monitored at home (e.g. blood loss, threatened premature labor, hypertension with indication for intravenous medication).
- The number of eCTG measurements assessed successful at closure by HCP.
- The number of eCTG measurements prematurely closed by HCP before complying the criteria of a successful measurement (7.1.1).

- Maternal and fetal factors HCPs have included in their assessment of the eCTG measurement (e.g. GA, fetal growth, Doppler measurements, PPRM).

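### Section 9.1 counts every minute with an FHR value as good signal, so an unrecognised display of the maternal rate as FHR can help a recording pass the 20% criterion, and nothing counts it

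*Protocol*

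**What the plan says.** - **Measure.** Section 9.1: "Signal quality will be defined as the percentage of time (minutes) in which the remote eCTG device delivers an FHR value". Nothing in that section asks whether the delivered value comes from the fetus.
- **Known failure mode.** Section 6.4.4 introduces it with "In rare cases, the amplitude of the fetal ECG signal": when the fetal signal on the abdomen is about as large as the maternal one, the two rates may be interchanged. It continues: "The system will then temporarily display FHR values as maternal heart rate and maternal heart rate values as FHR".
- **When loss is measured.** Section 7.1.1 says that recording duration and signal loss "will be derived from the recordings during the analysis phase of the project, i.e. not during the measurements".
- **Definition of success.** Section 7.1.1 lists three items: at least 30 minutes of registration, at most 20% signal loss, and interpretability in the professional's judgement. Section 9.1 refers to 7.1.1 but words the criterion as "at least 30 minutes interpretable signal quality and/or less than 20% signal loss during 30 to 90 minutes measurement". The introduction has: "Success rate is defined as maximum of 20% signal loss of total recorded time or at least 30 minutes of sufficient CTG interpretability".
- **What is recorded.** The nearest item in section 7.1.2 is "Number of switch to conventional CTG needed because of poor signal of remote eCTG measurement and possible cause". Section 2.2 also collects possible causes of poor signal quality when a measurement is repeated, and reasons for switches.

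**The concern.** The primary endpoint rests on signal loss, and signal loss is the complement of time with an FHR value. A minute in which the maternal rate is shown as FHR is useless for fetal assessment, yet it adds to the numerator of signal quality. Dropped signal counts against a recording; wrong-source signal counts in its favour.

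The check that remains is the professional's live reading, and an interchange that goes unnoticed has by definition passed that check. At stake is whether the success rate reflects usable fetal signal, and whether the report can say how often interchange occurred. The second matters because the study is a step towards monitoring at home.

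**Working it through.** The protocol gives no rate or duration for interchange, so there is no figure of its own to reproduce. The check has three parts.

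**1. Does any stated safeguard remove interchanged minutes from good signal?**

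- *Device suppression (6.4.4).* FHR output is withheld when fetal ECG quality is too low or when the output repeatedly fails a quality check. The text does not say that this detects interchange, which it lists as a separate warning.
- *Exclusion criteria (4.3).* Fetal and maternal arrhythmias are excluded, which deals with the irregular-ECG warning. No criterion deals with interchange.
- *Professional's interpretation (7.1.1).* This can fail a recording if the interchange is recognised. Under the *or* of the introduction and the *and/or* of 9.1, low signal loss can suffice without it.
- *Independent reference.* Synchronised Doppler covers 24 women and starts on day 2 (5.1), so it does not cover the day-1 primary recording.

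An unrecognised interchange therefore passes under every version of the definition. A recognised one can fail under 7.1.1.

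**2. How much interchange would change a recording's result?**

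Let L be the apparent loss and s the share of delivered minutes that are interchanged. Then

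usable-signal loss = 1 − (1 − L)(1 − s).

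This exceeds 20% when s > 1 − 0.80/(1 − L).

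| Apparent loss L | Share s needed | In a 30-minute recording |
|---|---|---|
| 0% | 1 − 0.80/1.00 = 20% | more than 6 of 30 delivered minutes |
| 10% | 1 − 0.80/0.90 = 11.1% | more than 3 of 27 |
| 15% | 1 − 0.80/0.85 = 5.9% | more than 1.5 of 25.5 |

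An illustrative borderline case is 5 minutes lost and 2 interchanged. The apparent loss is 5/30 = 16.7%, which passes; the usable-signal loss is 7/30 = 23.3%, which does not. A clean recording would need far more interchange to change sides.

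**3. What would that do to the success rate?**

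Section 4.4 plans on 90% of 60, that is 54 successes.

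- One woman reclassified: 53/60 = 88.3%, a change of 1/60 = 1.7 points.
- Three reclassified: 51/60 = 85.0%.
- Six reclassified: 48/60 = 80.0%.

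How many would be reclassified is unknown. If, purely as an assumption, 1% to 5% of day-1 recordings contained interchange, 0.6 to 3 women would be affected. The change would then be at most 1 to 5 points, and only if every affected recording crossed the limit.

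**The case against.** A reader might infer that interchange automatically scores as success and goes entirely unmonitored. The documents do not support that. Section 7.1.1 lists professional interpretability alongside the loss limit, trained staff watch the trace in real time (5.1, 7.3.2), and the device also outputs the maternal rate (6.1), which gives them something to compare. A recognised episode can fail the recording, and it has places to appear: the causes of repeats and switches (2.2, 7.1.2), and adverse-event reporting if it leads to an undesirable experience (8.2.1). What is missing is a dedicated count.

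A reader might also infer a material upward bias. The protocol calls the event rare and temporary, and part 2 of the working shows that a short episode changes the result only when a recording is already close to the limit. The realistic effect in 60 women may be nil.

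Three further points have weight:

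- The objective is feasibility, not FHR accuracy, with a CE-marked device in its intended use. That is a reason to leave the primary definition alone.
- Coinciding fetal and maternal rates are not the failure described, which is an exchange of the two. A rule that flags mere coincidence would over-count.
- Failing a recording afterwards denies the woman the extension to 90 minutes or the same-day repeat that the protocol allows, so a corrected rate would be biased downwards.

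Artefact handling could also be left to a statistical analysis plan. However, the protocol itself fixes the measure in 9.1, and as fixed it cannot separate fetal from maternal output.

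**Conclusion.** The point holds in a limited form. Signal quality as defined credits minutes in which the maternal rate is displayed as FHR. On the 20% criterion, an unrecognised interchange can act only towards success. Recognised interchange may be caught under 7.1.1 and may appear as the cause of a repeat or switch, but no parameter counts it.

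The direction follows from the definition. The size cannot be derived from the protocol and may be near zero: 1.7 points per woman reclassified, and a recording is reclassified only if interchange fills more than about 6% to 20% of its delivered minutes, at 15% down to 0% apparent loss. The 1% to 5% range is an assumption that shows scale, not an estimate. This justifies a count and a sensitivity analysis, not a new primary endpoint.

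**What to change.** Keep the primary definition and make three additions:

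1. In the analysis-phase extraction already planned in 7.1.1, compare the stored FHR and maternal heart-rate outputs by a prespecified rule for suspected interchange. The rule should look for an exchange of the two rates, not for moments when they merely coincide.
2. Add to 7.1.2 the number of recordings, and of minutes, flagged by that rule.
3. Add to section 9 a sensitivity analysis of the primary success rate that counts flagged minutes as signal loss, shown beside the primary result.

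The material is already there: raw recordings are kept (11.1), and section 9.3 already plans joint analysis of fetal and maternal beat-by-beat rates.

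The cost is protocol wording and a little extra signal processing. Detection will be imperfect, because day 1 has no independent reference. The sensitivity rate may be slightly less favourable, partly because reclassified women had no chance of an extension or same-day repeat; the report should say so.

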#### c. Safety assurance

To be sure that the safety of mother and child is guaranteed, a switch to the conventional CTG can be made at any time by the responsible clinician. If registration of FHR and/or EHG is insufficient without options for optimization of the signal, it can be decided to switch to the conventional CTG, which is available at the obstetric ward or outpatient clinic. This will not endanger mother and child

[NRM Link](#), NRM Link Charger and NRM App are parts of Nemo Remote® (NRM). Nemo Remote® is classified as class IIb, following Rules 10 and 11 of Chapter III of Annex VIII as well as implementation rules 3.3 and 3.5 of the Medical Device Regulation EU Regulation 2017/745.

[Nemo Patch](#) is an accessory of Nemo Remote®, classified as Class I medical device according to rule 1 of Annex VIII of the Medical Device Regulation EU Regulation 2017/745.

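### Section 9.1 can score a first-day eCTG as successful on fetal heart rate alone, even if it was replaced because the uterine signal was inadequate

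*Protocol*

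**What the plan says.** Section 9.1 of the protocol bases signal quality on one channel: "Signal quality will be defined as the percentage of time (minutes) in which the remote eCTG device delivers an FHR value". It counts a first-day recording as successful with "at least 30 minutes interpretable signal quality and/or less than 20% signal loss during 30 to 90 minutes measurement". The subsection of section 1 on remote eCTG also offers two routes: "Success rate is defined as maximum of 20% signal loss of total recorded time or at least 30 minutes of sufficient CTG interpretability".

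Section 7.1.1, to which 9.1 refers, lists three items together: at least 30 minutes of registration, "Including overall a maximum of 20% signal loss", and "Sufficient interpretability according to HCPs clinical interpretation". It does not name the signal whose loss is meant. It adds that signal loss is calculated from the recordings at the analysis stage, not at the bedside.

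Section 12.1c covers both channels: "If registration of FHR and/or EHG is insufficient without options for optimization of the signal, it can be decided to switch" to conventional CTG. Section 7.1.2 lists as a secondary parameter: "Number of switch to conventional CTG needed because of poor signal of remote eCTG measurement and possible cause".

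The Summary describes the primary outcome through the need to switch because of signal loss. Section 1 adds that feasibility includes whether no switch for interpretability was needed. Section 7.3.2 calls a first-day eCTG that is still not interpretable after repetition unsuccessful, and says a switch follows.

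**The concern.** Sections 1 and 6.1 describe the eCTG as delivering FHR, maternal heart rate and uterine activity, with uterine activity derived from the EHG as a separate output. The protocol accepts that an insufficient EHG may lead the clinician to replace the recording. The numerical route to success does not look at the EHG, and no section gives a loss measure or limit for it. Because 9.1 and section 1 make that route an alternative to clinical judgement, a recording the clinician replaced can still be credited afterwards from its FHR trace.

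The trial asks whether self-administered eCTG can serve without falling back on conventional CTG. If replaced recordings count as successes, the primary rate answers a narrower question. It may also fail to reconcile with the number of poor-signal switches reported beside it.

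**Working it through.** **Inputs.** The signal measure and the success rule come from 9.1, the alternative rule from section 1, the three listed criteria from 7.1.1, the handling of failure from 7.3.2, and the switch text from 12.1c. N = 60 and the 90% success rate come from 4.4.

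**Step 1: a test case.** Take a first-day recording of 30 minutes. FHR loss below 20% means FHR present for more than 0.80 × 30 = 24 minutes. Suppose this holds, the EHG is insufficient and cannot be improved, and the clinician uses the discretion in 12.1c to switch.

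| Text applied | Score |
|---|---|
| 9.1, signal-loss route | Success: FHR loss is under 20%, and the switch is not part of the rule |
| Section 1, signal-loss route | Success, for the same reason |
| 7.1.1, all three items required, and the clinician finds the trace uninterpretable without EHG | Not successful |
| 7.3.2, still uninterpretable after the repeat | Not successful |
| Summary, switch needed because of signal loss | Undetermined: it does not say whether EHG loss is meant |
| 7.1.2 | Recordable as a switch for poor signal |

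The same recording is a success under two statements of the rule and a failure under two others. The result turns on two points the protocol leaves open or contradicts: whether interpretability is required or optional, and whether missing EHG makes an eCTG uninterpretable.

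**Step 2: the plan's own figure.** For 54/60 = 0.90, the simple normal approximation gives a lower 95% limit of 0.90 − 1.96 × √(0.90 × 0.10/60) = 0.824, close to the 82.5% in 4.4. The Wilson method that 4.4 names gives 79.9% (two-sided). That mismatch is a separate matter and does not affect this point. Wilson limits are used below because they are the protocol's named method.

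**Step 3: size per woman.** One woman rescored from success to failure is 1/60 = 1.67 points. With x successes, p = x/60, n = 60 and z = 1.96, the Wilson limits are [p + z²/2n ± z√(p(1−p)/n + z²/4n²)] / (1 + z²/n).

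| Rescored | Rate | Wilson 95% CI |
|---|---|---|
| 0 | 54/60 = 90.0% | 79.9 to 95.3% |
| 1 | 53/60 = 88.3% | 77.8 to 94.2% |
| 2 | 52/60 = 86.7% | 75.8 to 93.1% |
| 3 | 51/60 = 85.0% | 73.9 to 91.9% |
| 4 | 50/60 = 83.3% | 72.0 to 90.7% |

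For x = 51: (0.85 + 0.0320 ± 1.96 × √(0.002125 + 0.000267)) / 1.0640 = (0.8820 ± 0.0959)/1.0640, which is 0.739 to 0.919.

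The number rescored is an assumption. Nothing in the protocol says how often FHR is adequate and EHG is not.

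**The case against.** The best reply is that 9.1 refers to 7.1.1, where clinical interpretability stands beside duration and signal loss. If all three items are required, a clinician who finds the tracing inadequate for want of EHG records a failure, and 7.3.2 says the same. On that view the real fault is the and/or wording, and the EHG case is one consequence of it. This is largely right and shapes the remedy. It does not remove the point, because 9.1 and section 1 state the alternative in so many words, and no section says that missing EHG makes a recording uninterpretable.

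An FHR-based loss measure is also defensible. Section 6.4.4 names FHR loss between 27 and 36 weeks as the known problem, and the limits in 7.1.1 cite a study of signal loss in FHR monitoring. That stands: FHR may remain the loss measure.

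The operating procedure and any SAP are not shown and may say which channel counts. They could add detail, but the protocol would still state conflicting rules.

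A reader might infer more than the text supports:

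- **That EHG failure forces a switch.** Section 12.1c only allows one, and only when the signal cannot be improved.
- **That 7.1.2 expressly counts EHG switches as poor signal.** It does not name the EHG; such a switch can merely be recorded there.
- **That 6.4.4 shows EHG failure to be common.** Its warning concerns, in limited cases, apparent activity unrelated to contractions, which is not lost signal.
- **That a reported 90% would really be 85%.** This assumes three such women, none caught by the interpretability judgement or resolved by the same-day repeat.
- **That the primary endpoint needs its own EHG threshold.** That is a design choice the documents do not settle.

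**Conclusion.** The point holds as a conflict between definitions. As written, 9.1 and section 1 allow a first-day recording with adequate FHR that was replaced for inadequate EHG to count as a primary success, against the Summary, section 1's own aim of no switch, and 7.3.2. The conclusion rests on two readings: that signal loss means loss of FHR, which follows from 9.1's definition of signal quality but is never stated outright, and that the and/or in 9.1 is applied literally.

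Measured against success as an interpretable eCTG with no switch for signal, this route can only raise the reported rate, by 1.7 points per woman affected. The number affected cannot be known from the protocol and may be zero.

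**What to change.** Reconcile 7.1.1, 9.1, section 1 and 12.1c by stating that:

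1. signal loss is the share of recorded time without an FHR value;
2. clinical interpretability of the eCTG is required in addition to the signal-loss limit, not as an alternative to it;
3. a first-day switch to conventional CTG recorded as due to insufficient signal, FHR or EHG, after the permitted repeat counts as not successful.

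Report the FHR-only success rate as a supporting figure, and tabulate poor-signal switches by channel from the cause that 7.1.2 already collects. This concerns only how recordings are scored. When to switch stays with the clinician as the protocol has it.

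The cost is protocol wording and making sure the recorded cause names the channel. N = 60 does not change. The primary rate may be slightly lower.
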